##### Intensity of the utilization of the StopBlues program by its users

The intensity of the utilization of the StopBlues program by its users will be assessed through a complementary set of measures. They include the number of downloads and connections to the StopBlues program, the time-lapse between the registration and the last connection to the program; the proportion of users who were made aware of the program through the different communication channels (such as communication by their local authority, a relative, GP’s waiting room, etc.) and the proportion of users who subscribed for a relative and not for themselves. The last two measures will be assessed at the first connection to the StopBlues program (T0) by an ad hoc questionnaire. Finally, we will measure the proportion of users who completed a safety plan at 12 and 24 months (Table 2).

**Table 2 Tab2:** Measures, data collection methods and timeframe

Measure	Data collection method	Periodicity of collection^**a**^							
		M0		M1	M2	M3	M6	M12	M24
*Outcomes measured at the cluster level*									
Number of deaths by suicide and suicide attempts	Database of the epidemiology center for medical causes of deaths for deaths by suicide and extraction from the French National Hospital Discharge Database and the *Oscour* database recording visits to emergency departments for suicide attempts	X						X	X
Fixed costs for the development of the promotion tools and semi-fixed costs for the implementation of the tailored intervention	Data collected by the research team and local authorities							X	X
*Outcomes measured among users of the StopBlues program*									
		**T0 or M0**	**T0’**^b^	**T1**	**T2**	**T3**	**T6**	**T12** **or** **M12**	**T24 or M24**
Number of downloads and connections	Software analytics							X	X
Length of use (time-lapse between the registration and the last connection)	Software analytics							X	X
Proportion of users hearing about the StopBlues program through the different communication channels	Ad hoc questionnaire	X							
Proportion of users who registered for a relative and not for themselves	Ad hoc questionnaire	X							
Proportion of users who completed a safety plan	Software analytics							X	X
Level of psychological distress	GHQ-12	X		X	X	X	X	X	X
Level of depression^c^	PHQ-9	X		X	X	X	X	X	X
Level of anxiety^c^	GAD-7	X		X	X	X	X	X	X
Level of suicidal risk^b^	MINI suicidality module		X	X	X	X	X	X	X
Level of a relative’s depression (for users coming for a relative and not for themselves)	MADRS	X							
Level of health-related quality of life	SF-12	X		X	X	X	X	X	X
Help-seeking behaviors and participation in supportive activities	Ad hoc questionnaire adapted from the General Help-seeking Questionnaire (GHSQ)	X		X	X	X	X	X	X

*GAD-7* 7-item General Anxiety Disorder, *GHQ-12* 12-item General Health Questionnaire, *MADRS* Montgomery-Asberg Depression Scale*, PHQ-9* 9-item Patient Health Questionnaire*, SF-12* 12-item Short Form health survey

^a^M0, M1, etc. refer to the time-lapse in month to the launch of the intervention while T0, T1, etc. refer to the time-lapse in month to the first connection of the user to the StopBlues program

^b^T0’ corresponds to the first time that the MINI suicidality module is submitted to the user (this only happens if the user has a bad score at the PHQ-9 and/or at the GAD-7 and/or for the Likert scales of the mood-tracking system which are not used in the evaluation) so T0’ can, therefore, differ from T0. In the case of the level of suicidal risk, T1, T2, T3, T6, T12 and T24, therefore, corresponds to the time after T0’ and not T0

^c^Depression and anxiety will be measured if the GHQ-12 score suggests potential psychological distress

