## Methods/design

### Study design

This study will be implemented as a three-arm, parallel-group, cluster-randomized controlled superiority trial, with before-and-after observation. Cluster-randomization was deemed mandatory because of potential contamination issues. Indeed, the very nature of the intervention assessed (i.e., a promotion program) cannot be applied at the individual level. This is typically a cluster-cluster intervention, as defined by Eldridge et al. [32]. Clusters were defined as geographical areas sharing a common local authority. These local authorities can either be cities or a grouping of cities (“*communautés de communes*” or “*communautés d’agglomérations*”) based on the local health governance of each area. If several adjacent local authorities volunteer individually to participate in the trial, they will be considered as a unique local authority.

Clusters will be randomly assigned to one of the following three arms with a ratio of 1:1:1:
Arm 1: no promotion of the StopBlues program (*control group*)Arm 2: promotion of the StopBlues program by local authorities only (*basic promotion group*)Arm 3: promotion of the StopBlues program by local authorities with an additional passive involvement of GPs through their waiting rooms (*intensified promotion group*)

The initial trial duration will be of 12 months. Baseline data on the number of suicidal acts, collected 12 months prior to the intervention, will also be considered in each cluster. After a 12-month post-randomization period, clusters from the control group will be allowed for a further 12-month period to launch their promotional campaign supported by the research team through regular contacts and additional technical and financial resources in comparison to arms 2 and 3 (*more sustained promotion by local authorities*). This will facilitate the recruitment of clusters as well as their adherence to the intervention during the first 12-month period [33]. It will also enable us to determine whether promotion led by local authorities could be improved by supporting them in the provision of additional promotional resources.

A complete description of the different steps of the trial is presented in Fig. 1 using the Timeline cluster tool of Caille et al. [34].

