## Trial status

The protocol reported here corresponds to the version of 1 September 2018. The intervention of the PRINTEMPS study was launched in April 2018 and the recruitment of potential users of the StopBlues program is taking place until March 2020.

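### Length of use and safety-plan completion have no fixed per-user window and no named clock, so the 24-month figures can differ by arm through registration timing alone

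*Protocol article*

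**What the plan says.** In the Protocol article, the section on intensity of utilization defines length of use as "the time-lapse between the registration and the last connection to the program". It adds that "we will measure the proportion of users who completed a safety plan at 12 and 24 months". In Table 2 both come from software analytics and are marked only in the 12- and 24-month columns.

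For user-level outcomes those columns are headed T12 or M12 and T24 or M24. The table note explains the labels: "M0, M1, etc. refer to the time-lapse in month to the launch of the intervention", whereas T0, T1 and so on "refer to the time-lapse in month to the first connection of the user to the StopBlues program". Neither row is tied to one of the two clocks.

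Three other sections bear on the point:
- **Trial status:** the launch is dated to April 2018, and entry is rolling over about 24 months from then, since "the recruitment of potential users of the StopBlues program is taking place until March 2020".
- **Study design:** "After a 12-month post-randomization period, clusters from the control group will be allowed for a further 12-month period to launch their promotional campaign".
- **Statistical considerations:** user-level secondary outcomes go into mixed repeated-measures models that include all users whatever their adherence, adjusted for initial distress and demographics. Time available since registration is not mentioned.

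**The concern.** The time from registration to last connection can never exceed the time from registration to the data cut. If the cut is a calendar date, someone who joined a month before it cannot score more than a month, however engaged they are. The capped value enters the data as an ordinary observed number, so a mixed model's tolerance of missing values does not help. Safety-plan completion has the same problem, because a late registrant has had less time to complete one.

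This would cancel out if users in all arms arrived at the same times. At 24 months they probably do not, because the control areas' own campaign starts a year after the others. Intensity of utilization is a stated secondary objective, and length of use is the first secondary outcome named in the abstract. A difference in arrival dates could be reported as a difference in engagement, to the disadvantage of the arm promoted later.

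**Working it through.** The article gives no expected length of use, so there is no figure of its own to reproduce. What can be checked is how far the definition separates two arms with the same true use.

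**Inputs from the article.** Entry runs from April 2018 to March 2020, about M0 to M24. Control promotion starts after M12. The measure is read at 12 and 24 months.

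**Assumptions.** True length of use U is exponential with mean m months and is the same in every arm. Registration is uniform over the stated period. Users connect often enough that a user still active at the cut has a last connection close to it.

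**Formula, launch clock.** With F the time from registration to the cut, the observed length is min(U, F). For F uniform on (a, b):

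E[min(U, F)] = m × {1 − [m/(b − a)] × (e^(−a/m) − e^(−b/m))}

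**M24 cut, registration over M0-M24 (F on 0-24) versus M12-M24 (F on 0-12):**
- m = 3: 3 × {1 − (3/24)(1 − e^−8)} = 2.63, against 3 × {1 − (3/12)(1 − e^−4)} = 2.26; 14% lower.
- m = 6: 6 × {1 − (6/24)(1 − e^−4)} = 4.53, against 6 × {1 − (6/12)(1 − e^−2)} = 3.41; 25% lower.
- m = 1: 0.96 against 0.92; 4% lower.
- m = 12: 6.81 against 4.41; 35% lower.

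**Sensitivity to registration pattern, M24 cut:**
- If the promoted arm registers only over M0-M12 (F on 12-24), its means for m = 1, 3, 6, 12 are 1.00, 2.99, 5.65 and 9.21. Against 0.92, 2.26, 3.41 and 4.41, the gap runs from 8% to 52%.
- The program is open to control areas from the start, so some control users will register early. If 20% register over M0-M12, the control mean is 0.2 × 2.99 + 0.8 × 2.26 = 2.41 for m = 3, and 0.2 × 5.65 + 0.8 × 3.41 = 3.86 for m = 6. Against 2.63 and 4.53, the gap falls to 8% and 15%.

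**Safety plan, M24 cut.** Assume a 6-month mean time to completion among users who would eventually complete one. The proportion complete at the cut is E[min(U, F)]/m, which is 4.53/6 = 75% (M0-M24) against 3.41/6 = 57% (M12-M24).

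**User clock.** The definition itself does not shorten a late registrant's use. If data close near M24, however, nobody who registers after M12 can be followed to T12, and only users who register at launch reach T24. If everyone is kept regardless, with m = 6, users registered over M0-M12 have a full 12-month window and average 6 × (1 − e^−2) = 5.19. Those registered over M12-M24 average 3.41.

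**After the change.** With a closed window of w months and only users who have the full window, the expected value is m(1 − e^(−w/m)). For m = 3 and 6 this gives 2.59 and 3.79 with w = 6, and 2.95 and 5.19 with w = 12, in every arm. Registration date no longer enters.

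**The case against.** The strongest objection is that a calendar cut is not stated. A reader might infer one from the 12- and 24-month columns, but the column heads allow either clock. The layout leans towards the launch clock: the questionnaire rows also carry marks at the earlier user-clock times, the software-analytics rows do not, and Table 1 counts downloads by zip code. That is a hint and not a rule, so this objection stands. It does not remove the problem, since the user clock leaves incomplete windows for late registrants if data close near M24.

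A second tempting inference is that the arms already differ at 12 months. The article does not support it. Delayed control promotion cannot act before month 12. The freedom to tailor campaigns applies equally to both promoted arms, and a single launch date is given. Late registrants are still capped at an M12 cut, but nothing shows that this differs by arm.

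Third, censoring rules may sit in an analysis plan that is not shown. That is possible, and it is why the point concerns the definition and timing printed here and not the absence of a rule.

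Fourth, the sections on long-term effectiveness and on the sustained promotion name only deaths and attempts, so no 24-month contrast on length of use is spelled out. However, Table 2 collects the measure at 24 months, and the abstract says the later promotion is assessed with the same outcome measures.

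Finally, this is one of several usage measures under a secondary objective. The primary outcome is untouched.

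**Conclusion.** The point holds in a limited form. Neither row has a fixed window or an assigned clock. If the launch clock applies, length of use and safety-plan completion at 24 months depend on registration date, and the delayed control promotion makes that dependence likely to differ by arm. With identical true use, the illustrative gap is 2.6 v 2.3 months (3-month mean) or 4.5 v 3.4 months (6-month mean). It is about 4% if mean use is one month, and larger if use is long or the registration periods do not overlap. These sizes rest on assumed exponential use and uniform registration; the article supplies neither. If the user clock applies, the difficulty is incomplete follow-up of late registrants, assuming that data close near M24. To call the arms non-comparable in general, or biased in the first year, would go further than the article allows.

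**What to change.** State for both rows which clock applies. Then take one of two routes:
- **Closed window.** Measure both over the same fixed number of days from registration: length of use truncated at that number, and safety plan completed within it. Include only users whose full window falls before the cut. The window needs an upper limit. An open-ended measure, such as any connection after a given day, still favours early registrants.
- **Censoring.** Analyse time to last use, with users still active near the cut treated as censored, and state in advance how recent a connection counts as still active.

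Keep the raw time-lapse as a descriptive figure.

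The cost is wording only, because computing length of use already requires registration and connection dates. The price of the closed window is that users who register too close to the cut are left out of that measure. A longer window excludes more of them, and they would come disproportionately from the arm promoted later.

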##### Help-seeking behaviors and participation in supportive activities by users of the StopBlues program

Help-seeking behaviors (towards health professionals or lay individuals) and participation in supportive activities by users of the StopBlues program will be assessed using an ad hoc questionnaire adapted from the General Help-seeking Questionnaire (GHSQ) [45] at users’ first connection (T0) and then regularly until the end of the intervention (Table 2).

##### Level of psychological impairment of users of the StopBlues program

Several outcome measures will be considered to assess the effect of the intervention on the level of psychological impairment of users of the StopBlues program. They include psychological distress, level of depression, anxiety and suicidal risk (including a past history of suicide attempts). They will be measured using the 12-item General Health Questionnaire (GHQ-12) for psychological distress [46], the Patient Health Questionnaire (PHQ-9) for the level of depression [47], the seven-item Generalized Anxiety Disorder-7 (GAD-7) for the level of anxiety [48] and the Mini International Neuropsychiatric Interview (MINI) suicidality module for the level of suicidal risk [49]. All questionnaires have previously been used in the French language and are estimated to have good measurement properties [50–59]. The level of psychological distress will be measured at the first connection of the user to the StopBlues program (T0) and then regularly until the end of the intervention (see Table 2). Depression and anxiety levels will be measured for users having a GHQ-12 score suggesting potential psychological distress. Users will also have to indicate their overall mood level through a mood-tracking system including three simple Likert scales ranging from 0 (worst possible) to 100% (perfect). These will focus respectively on users’ global health, mood and overall level of energy. These scales will not be considered in the evaluation of the level of psychological impairment of users of the StopBlues program but will condition the measurement of suicidal risk. The suicidal risk will indeed only be measured if the score of the PHQ-9 questionnaire is superior or equal to 10, or if the score of the GAD-7 questionnaire is superior to 7, or if the score on one of the scales of the mood-tracking system is inferior or equal to 40% or inferior or equal to 50% with a 20% decrease in comparison to the previous score. The suicidal risk will be measured at T0’ (see Table 2) and then regularly until the end of the intervention. Where the user has registered with the StopBlues program for a relative and not for themselves, they will be asked to fill in the Montgomery-Asberg Depression Scale (MADRS) [60] at the first connection (T0).

#### Long-term effectiveness of the intervention

The long-term effectiveness of the intervention will be measured by the numbers of deaths by suicide and suicide attempts (in contact with the healthcare system other than primary care only) considered separately during the 24 months following the start of the intervention.

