#### Secondary objectives

The secondary objectives will be measured both at the cluster level (geographical area sharing a common authority) and among users of the StopBlues program.

Secondary objectives considered at the cluster level are as follows:
To assess the cost-effectiveness and to run a budgetary impact analysis of the intervention

Secondary objectives measured among users of the StopBlues program are as follows:
2.To assess the effectiveness of the intervention in terms of the intensity of the utilization of the program3.To assess the effectiveness of the intervention for help-seeking behaviors and participation in supportive activities (any activity that a user finds beneficial for their mental health)4.To assess the effectiveness of the intervention for the evolution of the level of psychological impairment

It should be noted that an additional form of promotion (more sustained promotion by local authorities, described below) will be implemented after 12 months in the control group and evaluated using the same primary outcome measure. In parallel, the long-term effectiveness of the two main types of local promotion (with or without a passive involvement of GPs through their waiting room) will also be assessed.

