Target sample size	34 clusters for a total of more than 4 million adult inhabitants
Recruitment status	On-going
Primary outcome	Number of suicidal acts at the cluster level during a 12-month period, including deaths by suicide and suicide attempts. Data will be extracted from administrative databases.
Key secondary outcomes	Number of deaths by suicide and suicide attempts during a 24-month period Cost-effectiveness and budgetary impact analysis: fixed costs for the development of the promotion tools, semi-fixed costs for the implementation of the intervention, costs of suicidal acts, level of health-related quality of life and associated utility (validated questionnaire). For participants who used the StopBlues program: Effect on the intensity of the utilization of the StopBlues program by its users: number of downloads and connections for each zip code corresponding to local authorities included in the trial, time-lapse between the registration and the last connection to the StopBlues program for each user, proportion of users who came to know the program through the different communication channels, proportion of users who registered for a relative and not for themselves, proportion of users who completed a safety plan. Effect on the help-seeking behaviors of users of the StopBlues program and their participation in supportive activities: help-seeking and participation in supportive activities collected with an ad hoc questionnaire adapted from a validated one. Effect on the level of psychological impairment of the users of the StopBlues program: level of psychological distress, depression, anxiety, suicidal risk (validated questionnaires) (see Table 2 for more details)
Ethics review	Approved by the Ethics Committee of the French National Institute for Health and Medical Research (Approval n° 15–240 of 7 of July 2015). Approved by the French Advisory Committee for Data Processing in Health Research (Approval n° 15–793 of 30 September 2015). Approved by the French Data Protection Authority (Decision DR-2016-421 of 3 November 2016)

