### Sample size and power

The number of clusters was fixed by the identification of 34 clusters that agreed to be involved in the trial. The proportion of inhabitants who died from suicide or who made suicide attempts over a 12-month period was estimated to be 0.215% (personal data). We used an expected rate of 0.190% in the experimental group, which represents a reduction of 11.6%, slightly higher than the 10% global target supported by WHO for interventions on suicide [10]. In a two-arm, individually randomized trial, this would lead to a required number of participants of 1,229,350 to achieve a power of 80% with a Type I error rate of 2.5%. Type I error is set at 2.5% because two experimental groups are compared to the control group. Clustering also has to be taken into account. As the number of voluntary clusters was fixed, we calculated what the intraclass correlation coefficient (ICC) would be in order to achieve a power of 80% with our pre-specified number of clusters. Although we acknowledge that such an approach is not classical, it enables us to take into account feasibility reasons. Our mean cluster size equals 138,172 inhabitants and, therefore, randomizing 11 clusters in each arm allows for achieving 80% power if the ICC is around 10^−5^. Although this is a very low ICC, one has to keep in mind that clusters are geographical areas and ICCs are known to be lower in large clusters as compared to small ones. Moreover, ICC is known to depend on prevalence [37], with small ICC values for prevalence close to 0 or 1, and we expect very low rates (about 0.2%). As a consequence, we considered that a 10^−5^ ICC value would be appropriate in our trial.

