### Outcomes

#### Primary outcome measure

The primary outcome measure will be the number of suicidal acts (both death by suicides and suicide attempts) during the 12 months after the start of the intervention. The number of deaths by suicide will be obtained from the Epidemiology Center for Medical Causes of Death (“*Centre d’épidémiologie sur les causes médicales de décès”*, CépiDc) while the number of suicide attempts will be approximated by the number of suicide attempts in contact with the healthcare system (other than primary care only). To estimate the number of suicide attempts seen in acute care, we will use the exhaustive French National Hospital Discharge Database (“*Programme de médicalisation des systèmes d’information en médecine, chirurgie, obstétrique*,*”* PMSI-MCO) [40]. To estimate the number of suicide attempts seen in emergency care, we will use the *Oscour* database which records visits to emergency departments [41]. Participants from clusters included in the study will be identified through their zip code of residence.

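### The long-term endpoint is a 24-month total that contains the primary 12 months, so it cannot show whether an effect lasts beyond year 1

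*Protocol article*

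**What the plan says.** The section on long-term effectiveness takes deaths and attempts as two outcomes, each "considered separately during the 24 months following the start of the intervention". Table 1 lists the same measure among the key secondary outcomes: "Number of deaths by suicide and suicide attempts during a 24-month period". The secondary objectives present this as a question in its own right: "In parallel, the long-term effectiveness of the two main types of local promotion" will also be assessed.

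The primary outcome is the composite of deaths and attempts "during the 12 months after the start of the intervention". Each long-term count therefore contains its own component of the primary count.

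Three other statements bear on the point:
- Under Study design and Intervention to be evaluated, the control clusters are offered a more sustained promotion from month 12. Its effect has its own 12-month window, starting when that promotion starts.
- Table 2 schedules the counts at M0, M12 and M24.
- Statistical considerations names a baseline-adjusted Poisson regression on cluster counts for the primary outcome, and a similar method for cluster-level secondary outcomes.

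**The concern.** Half of the 24-month window is the period already analysed for the primary outcome. On the total, different histories look the same. With the planned rate ratio of 0.884, full benefit in year 1 and none in year 2 gives 0.884 + 1 = 1.884 control-years of events. Half the benefit in both years gives 2 × 0.942 = 1.884. No model fitted to the total can tell these apart.

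At stake is a claim of durability. A positive 24-month result could be read as showing that promotion still works after its first year when it only repeats the year-1 finding. That matters because the decision to continue the intervention after the trial is to rest on its results. The reverse error is also possible: if the promotion arms lose their effect while the control arm gains from its own campaign, the total can look null and hide both changes.

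**Working it through.** **Inputs.** From Sample size and power: 12-month rates of 0.215% (control) and 0.190% (experimental), 11 clusters per arm, mean cluster size 138,172, ICC about 10^-5, 80% power, type I error 2.5%. From Background: 13.8 suicide deaths per 100,000. Assumptions: this national death rate applies to the clusters, which leaves 215 − 13.8 = 201.2 attempts per 100,000; the planned effect is the same for deaths and attempts; and the 2.5% level, the only one stated, is used for the long-term tests.

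**Reproducing the plan's figures.** With z = 2.241 (two-sided 2.5%) and 0.842 (80% power), n per arm = (2.241 + 0.842)² × [0.00215 × 0.99785 + 0.00190 × 0.99810] / 0.00025² = 614,675. Two arms need 1,229,350, as stated. The compatible ICC is (11 × 138,172 / 614,675 − 1) / 138,171 = 1.07 × 10^-5, also in agreement.

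**Method.** On the log rate ratio, SE² = (1/E0 + 1/E1 + 2·CV²)/11. E0 and E1 are expected 24-month events per cluster. CV² = ICC(1 − p)/p = 10^-5 × 0.99785/0.00215 = 0.00464 if cluster effects persist across both years, and half that if they are independent between years. The chance of declaring a benefit is Φ(ln(E0/E1)/SE − 2.241).

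**Attempts, effect in year 1 only, control unchanged in year 2.** Annual control events per cluster are 0.002012 × 138,172 = 278.0.
- E0 = 2 × 278.0 = 556.0 and E1 = 278.0 × 1.8837 = 523.7.
- Rate ratio 0.942; ln(E0/E1) = 0.0599.
- Persistent cluster effects: SE = 0.0344, z = 1.74, chance 31%.
- Independent cluster effects: SE = 0.0276, z = 2.17, chance 47%.

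The same calculation on the rate-difference scale gives 30-46%. Simulation of a baseline-adjusted cluster-level test gave 36-41%. A plain Poisson model with no allowance for overdispersion gave 71-75%, but the protocol does not say that overdispersion will be ignored.

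**Deaths, same scenario.** E0 = 38.1, E1 = 35.9, SE 0.073-0.076, chance 7-8%; 5-10% in simulation.

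**Attempts, allowing for the control arm's promotion in year 2 (ICC 10^-5).**

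| Year-2 rate ratio, control arm | Year-2 rate ratio, promotion arm | 24-month rate ratio | Chance of declaring a benefit |
|---|---|---|---|
| 1 (unchanged) | 1 (effect lost) | 0.942 | 30-47% |
| 0.942 (half the gain) | 1 (effect lost) | 0.970 | 8-13% |
| 0.884 (full gain) | 1 (effect lost) | 1.000 | about 1% |
| 0.884 (full gain) | 0.884 (effect kept) | 0.938 | 34-52% |

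In the third row the total is null although the arms differ in both years, in opposite directions. In the last row promotion does last, and only the contrast between arms disappears in year 2.

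**Months 13-24 alone.** If the arms do not differ in year 2, the chance of declaring a benefit is the nominal 1.25% in one direction.

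**The case against.** A cumulative count over 24 months is a recognised long-term measure, and it matches the 24-month horizon of the budget impact analysis. The protocol says long-term effectiveness and never uses the word durability. Deaths and attempts are already compared separately at 12 months, and Table 2 schedules counts at M12 and M24, so year 2 could be derived. This stands in part: the total is legitimate as a measure of cumulative benefit and need not be dropped. It does not remove the point, because the stated measure for the promotion arms is the total, in two places, with no year-2 measure beside it.

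A reader might infer something stronger: that a year-1-only effect would often be declared a long-term one, in some 42-60% of trials. The documents do not support that in general. It comes from all acts combined at p < 0.05 with an unchanged control rate. The plan analyses deaths and attempts separately, its only stated error rate is 2.5%, and the control arm starts its own promotion at month 12. Nor can the 11.6% be carried over to intensified versus basic promotion, since it was planned for an experimental arm against control.

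It is also fair to object that simply switching to months 13-24 would mislead. Against the control arm, that contrast compares two promoted groups. If promotion lasts and control catches up, it would be null and could be read as no long-term effect. This stands and shapes the fix.

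**Conclusion.** The point holds as one of structure: the 24-month total contains the primary window and cannot show whether an effect lasts beyond year 1, whichever arms are compared. Its frequency is conditional. About 30-47% for attempts requires the planned effect in year 1, none in year 2, an unchanged control rate, ICC 10^-5 and a two-sided 2.5% test. For deaths it is under about 10% on the same terms. For attempts it falls to about 8-13% or about 1% if the control arm's own promotion yields half or all of the planned gain in year 2. For intensified versus basic promotion no frequency can be given. The split between deaths and attempts rests on the national death rate, and the level for the long-term tests is an assumption.

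**What to change.** For deaths and for attempts, report rate ratios for months 1-12 and months 13-24 side by side, adjusted for the pre-trial year, with an arm-by-period term. The year-2 count is the M24 count minus the M12 count. Keep the 24-month total as a cumulative measure, and state that it will not be read as evidence of durability.

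Name intensified versus basic promotion as the year-2 contrast whose comparator does not change at month 12. Label every months 13-24 contrast with the control arm as a comparison with more sustained promotion, not with no promotion.

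The cost is a change of wording; Table 2 already schedules the data. Each period has fewer events than the total, so intervals will be wider, and no reporting change can supply an unexposed comparator in year 2.
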